### Blinding

It will not be possible to blind participants or clinicians to treatment allocation. The trial statistician and TSC will be blinded. To assess the potential impact of outcome assessment bias, an additional analysis of the primary endpoint will be performed, using an independent blinded adjudicated primary outcome concerning whether trial participants needed OHSS-related hospitalisation within 28 days.

### Trial monitoring and oversight

The trial will be overseen by a TSC and data monitoring and ethics committee (DMEC). Membership of both will consist of independent experts in the field and the TSC includes a patient representative. The DMEC may advise the chair of the TSC at any time if, in their view, the trial should be stopped for ethical or adaptive reasons.

Day-to-day running of the trial will be coordinated by the trial management group (TMG), consisting of the grant coapplicants, plus members of the Jessop Wing Fertility Unit, Sheffield CTRU and patient representatives.

### Sample size and interim analyses

Under current conservative management, the mean OHSS-related hospitalisation rate is approximately 41.2% (26/63) based on a retrospective audit of medical records of IVF patients across six IVF fertility units over a year (95% CI 29.0% to 54.4%). Earlier active management interventions based on uncontrolled small previous studies have resulted in low hospitalisation rates of around 0%–8%.^10 12 13 20^ As such, this trial is targeting a 20% absolute reduction in hospitalisation for OP to be considered superior to UC. This reduction is believed to be realistic as previous uncontrolled studies have observed similar or greater effects and, if observed, is more convincing to change clinical practice. A 20% absolute reduction translates to an OR of 0.3825 or relative risk/risk ratio (RR) of 0.512 assuming a 41% UC event rate. Thus, the targeted effect in terms of OR or RR is a function of the UC event rate whereas the targeted 20% absolute reduction is consistent across the plausible UC event rates. An updated preliminary health economics model (trial protocol, via ISRCTN71978064) has indicated that OP needs to achieve at least 4.7%–5.7% reduction in hospitalisation to become cost saving under several assumptions about the ratio of early to late OHSS and underlying UC hospitalisation rates assuming a 20% targeted reduction.

The aim of the trial is to gather convincing evidence to influence the effects of the early OP that is most likely to change practice regardless of the direction of results and so a group sequential design with an option for early stopping for futility (lack of benefit) is used.

The trial will require a maximum total sample size of ~224 (112 per arm) with an interim analysis when ~146 participants (73 per arm) have accrued primary outcome. This assumes a 90% power, one-sided 2.5% type 1 error, 41% UC hospitalisation rate, 0% drop-out rate, a 20% reduction in hospitalisation rate and a futility threshold of −4.5% (difference in hospitalisation rate). In this case, the trial will be stopped early for futility if the observed reduction in hospitalisation rate at an interim analysis is less than 4.5%. There is only a 1.9% chance of stopping the trial early for futility in error when OP is truly beneficial. Finally, there is a 72.2% probability of stopping early when the effect of OP is the same as UC (ie, 41% hospitalisation rate) (see online supplemental file 2).

10.1136/bmjopen-2023-076434.supp2Supplementary data

### Statistical analysis

Detailed of all analysis will be described in an open-access and prespecified SAP to be developed and signed off before accessing unblinded data.

The primary analysis will be an intention to treat, including all eligible participants randomised with informed consent. Baseline data will be summarised at the interim and final analyses by treatment group. The absolute difference in hospitalisation rates between arms is the primary summary measure of the treatment effect. RR and OR (estimated using a simple logistic regression model) will also be presented. At an interim analysis, the unadjusted difference in hospitalisation rates between arms will be calculated to inform the interim decision on whether to stop early for futility. For sensitivity analysis, a mixed effects logistic regression model adjusted for stratification factors (site as a random effect and OHSS severity as a fixed effect) and adjusted difference in hospitalisation rates will be obtained using the delta method via margins.^21^ For the final analysis of the primary outcome, the unadjusted difference in hospitalisation rates with CI obtained via normal approximation will be reported as well as the p value from a χ^2^ test. Stagewise ordering will be used for sensitivity analysis to obtain the median unbiased estimate of the difference in hospitalisation rates between arms with the associated 95% CI to be presented alongside the maximum likelihood estimate if the trial progressed beyond interim analysis. The details of additional sensitivity analyses to be performed adjusting for baseline covariates are found in the SAP. Reporting will adhere to the adaptive designs CONSORT (Consolidated Standards of Reporting Trials) Extension guidance.^22^

For progression of OHSS severity, a mixed effects logistic regression model adjusted for stratification factors (site as a random effect and OHSS severity as a fixed effect) will be used and an adjusted difference in hospitalisation rates will be obtained using the delta method via margins.^21^ Treatment effects will be presented as adjusted OR, adjusted risk difference and adjusted relative risk/RR with 95% CIs.

For time to resolution of OHSS assessed within 28 days postrandomisation, Kaplan-Meier curves will be used to visualise the resolution curves between treatment arms and differences qualified using a log-rank test. Median time to resolution by treatment arm with 95% CI will be calculated and reported as summary measures of within-group effects. Participants who fail to achieve resolution of symptoms within 28 days postrandomisation will be censored. Sensitivity analysis and alternative approaches when the proportional hazard assumption is not met will be detailed in the SAP.

For cumulative length of OHSS hospital stay, bootstrapping resampling procedure (accounting for stratification) will be used to obtain the median difference with 95% CI and associated p value. For patient satisfaction at 28 days, a total satisfaction score will be analysed using a mixed effects linear regression model adjusted for site (as a random effect) and OHSS severity (as a fixed effect), and the adjusted mean difference between treatment arms with 95% CI and associated p value will be presented.

Analysis of safety outcomes (eg, AEs and SAEs) will be based on descriptive statistics using the safety analysis population defined based on treatment-as-received population. Details of additional analysis accounting for repeated events and differential follow-up is found in the SAP.

Subgroup analyse will be performed to explore whether there is heterogeneity in treatment effect on the primary outcome across the following prespecified subgroups:

Baseline severity of OHSS (moderate or severe).Whether a participant is taking a preventative drug at randomisation (yes or no).Whether the participant has early or late OHSS at randomisation.Whether the OP procedure was done vaginally or abdominally. For participants who received multiple procedure (which may happen in few cases), this classification will be based on the first performed procedure.

A mixed effects logistic regression model that includes an interaction effect between preplanned subgroup and treatment group adjusted for site (as a random effect) and severity of OHSS (as a fixed effect) only if it is not a subgroup factor of interest will be used.

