OHSS-related exclusion criteria:Significant pain or vomiting requiring hospitalisation.Pulmonary embolism.When in the judgement of the clinician, the patient’s condition is severe enough to warrant admission to a high-dependency care unit (such as critical OHSS as defined in the RCOG green-top guidelines), and therefore, not suitable for outpatient management.Non-OHSS-related medical conditions: a concurrent medical condition requiring immediate inpatient management.Patients who have been previously randomised but later present with moderate or severe OHSS symptoms in subsequent cycles after their initial trial involvement.Participation in other trials involving ovarian stimulation or ovarian response.

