Some fertility units undertake other preventative measures (eg, dopamine agonists, gonadotropin-releasing hormone (GnRH) antagonists, cessation of IVF cycle) to reduce the risk of OHSS and details of these measures will be collected during the trial, along with information on the provision of care within the conservative management arm. Rarely, patients may be prescribed GnRH antagonists as treatment for established moderate or severe OHSS. This will not be prohibited for trial participants in both arms and data will be collected on GnRH use within the trial.

Participants may wish to stop study treatment, or there may be a clinical need to stop treatment. Participants randomised to the intervention arm, who withdraw from receiving the intervention will continue to be followed-up and will remain in the trial, unless they request to be withdrawn.

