OHSS-related hospitalisation for at least 24 hours within 28 days of randomisation.

Secondary outcomes:

Need for OHSS-related hospitalisation within 28 days—independent blinded central assessment.Time to resolution of OHSS assessed within 28 days of randomisation.Progression of OHSS severity within 28 days of randomisation.Cumulative length of OHSS-related hospitalisation.Live birth, pregnancy outcomes, neonatal death and serious adverse events (SAEs) including congenital abnormalities in the new-born within 13.5 months of randomisation.The occurrence of thrombosis, embolism and significant infections requiring antibiotic treatment or hospitalisation within 90 days of randomisation.AEs within 28 days of randomisation.Patient satisfaction assessed using the Client Satisfaction Questionnaire 8^19^ based on total scores at 28 days postrandomisation.EQ-5D-5L participant quality of life daily and at 28 days postrandomisation.Health resource use and patient costs at 28 days postrandomisation.

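### The primary set is called intention to treat but limited to eligible women, so its wording permits unblinded post-randomisation exclusions in an open-label trial whose outcome is hospital admission

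*Protocol article*

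**What the plan says.** The protocol article, Statistical analysis, defines the primary set: "The primary analysis will be an intention to treat, including all eligible participants randomised with informed consent". Three other parts bear on it.

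- **Exclusion criteria (Recruitment).** One is "Significant pain or vomiting requiring hospitalisation". Another rests on the clinician's judgement that the patient's "condition is severe enough to warrant admission to a high-dependency care unit". A third is "a concurrent medical condition requiring immediate inpatient management", which is listed as not related to OHSS.
- **Primary outcome (Outcomes).** "OHSS-related hospitalisation for at least 24 hours within 28 days of randomisation".
- **Blinding.** "It will not be possible to blind participants or clinicians to treatment allocation". Also: "The trial statistician and TSC will be blinded". A blinded independent adjudication is planned, but its question is whether the woman needed OHSS-related admission, not whether she was eligible.

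Under Intervention and control, women in the intervention arm "who withdraw from receiving the intervention will continue to be followed-up and will remain in the trial", unless they ask to be withdrawn. That covers stopping treatment. Nothing shown covers women found to be ineligible after randomisation.

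**The concern.** Intention to treat ordinarily means everyone randomised, in the arm allocated. Adding an eligibility condition makes membership of the primary set depend on a judgement that can be made or revised after allocation is known.

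In many trials this would be a minor matter, because ineligibility is an objective baseline fact. Here the pain-or-vomiting criterion is itself worded in terms of needing hospital care, and the outcome is a hospital stay. A woman admitted soon after randomisation could be recorded as a primary event or as someone who should never have been enrolled. Staff who would supply that judgement know her arm. If such reclassification fell more on one arm, events would be removed selectively, and both the primary risk difference and the interim futility comparison would shift.

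**Working it through.** **1. Design figures (Sample size and interim analyses).** Inputs: 41% versus 21%, one-sided 2.5%, 90% power, interim at 73 per arm, futility if the observed reduction is below 4.5 points.

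Per-arm size, pooled formula: [1.960·√(2·0.31·0.69) + 1.2816·√(0.41·0.59 + 0.21·0.79)]² / 0.20² = (1.282 + 0.818)² / 0.04 ≈ 110.3, so 111 per arm (222 in total), against the stated 224. At 112 per arm, power with the futility look is 90.2%. The chance of stopping at the interim under the target effect is Φ[(0.045 − 0.20)/√(0.4078/73)] = Φ(−2.07) = 1.9%, as stated. Under no effect it is 72.2% by binomial simulation, as stated. The design figures are not in dispute.

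**2. Who may remove a woman, and on what grounds.** The stated set requires eligibility. The article does not say that eligibility for analysis is fixed at randomisation, judged from pre-randomisation data only, or judged by someone blind to arm and outcome. The blinded statistician and TSC are not given that task. The blinded adjudication answers a different question and cannot return a woman already left out of the set.

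**3. Hypothetical size.** The article gives no rate of post-randomisation ineligibility, so everything here is an assumption: no true effect, 46/112 admitted in each arm, and k admitted women removed from OP only.

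Apparent reduction = 46/112 − (46 − k)/(112 − k). The test rejects when z = (p_UC − p_OP)/√[p̄(1 − p̄)(1/n_UC + 1/n_OP)] ≥ 1.96, with UC the usual-care arm. Error rates are by exact binomial enumeration without the futility rule. In model A both arms are Bin(112, 0.41) and k OP events are then removed. In model B UC is Bin(112, 0.41) and OP is Bin(112 − k, (46 − k)/(112 − k)).

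| k | OP after removal | Apparent reduction (points) | Error, A | Error, B | Error if k admitted women are removed from each arm (A) |
|---|---|---|---|---|---|
| 0 | 46/112 = 41.1% | 0 | 2.5% | 2.4% | – |
| 3 | 43/109 = 39.4% | 1.6 | 4.5% | 4.3% | 2.6% |
| 5 | 41/107 = 38.3% | 2.8 | 6.4% | 5.9% | 2.9% |
| 6 | 40/106 = 37.7% | 3.3 | 7.8% | 7.1% | 3.1% |

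As a third variant, each admitted OP woman is removed with probability 10% (about 5 women). This gives a 2.5-point false reduction and 5.7% error with the futility rule applied, or 5.8% without it. The futility rule therefore makes little difference.

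**4. Interim.** With 30/73 in each arm, removing 5 admitted OP women gives 30/73 − 25/68 = 4.3 points, below the 4.5-point threshold. Removing 6 gives 30/73 − 24/67 = 5.3 points, above it. Under this one-arm assumption, six removals would turn a stop into a continue.

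**The case against.** A reader might infer that ineligible women *are* dropped. The article does not say so. It describes no eligibility review after randomisation, and its Method and analysis section also uses *eligible* simply for the people who go on to be randomised. Read that way, the word describes who was enrolled and restricts nothing. This stands: the restrictive reading is literal but not the only one. On the harmless reading, though, the word is redundant and can go.

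A reader might also treat both judgement-based criteria as restatements of the outcome. Only the pain-or-vomiting criterion refers to hospitalisation generally. High-dependency care is a much higher bar than a stay of at least 24 hours, so overlap there is weaker. Both criteria describe the woman's state at entry, and day 0 symptoms and blood count (Table 2) give a record against which a later claim could be checked. That helps, but nothing in the article requires the check.

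A third tempting inference is that only OP women are seen daily and so are scrutinised more. Both arms keep daily diaries, and the Follow-up section lists visits without distinguishing arms. The difference lies in site review of diaries and in daily adverse-event questioning, and nothing links either to eligibility. The point does not rest on it.

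Finally, who judges eligibility and on what data is ordinary SAP content, and the SAP is not shown. That is fair for the procedure. The analysis set, however, is stated here, and a SAP that follows the wording inherits the problem.

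**Conclusion.** The point holds as one about a stated definition that is too permissive. The wording allows women to be left out of the primary analysis after randomisation, by staff who know the arm, on a criterion that overlaps the outcome. It does not establish that this is planned or likely.

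The error rates in the table are not a forecast. They rest on three assumptions: no true effect, removals from OP only, and every removed woman having been admitted. On those terms a handful of removals roughly doubles or triples the nominal 2.5%. Balanced removals produce no false difference in the worked example and leave the error close to nominal. The wording should be corrected, but neither the design nor the sample size is called into question.

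**What to change.** Delete *eligible* from the definition, so that all randomised participants who gave informed consent are analysed in the arm allocated, whatever is later found about eligibility. Use the same definition at the interim and final analyses, and check that the SAP agrees.

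If an eligible-only set is wanted, present it as a sensitivity analysis, with ineligibility judged only from data recorded before randomisation and by someone blind to arm and outcome.

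The primary change is one word, and the maximum stays at 224. The optional sensitivity analysis adds a small blinded review. The downside is slight dilution of the effect from a few ineligible women; the article gives no rate from which to quantify it.

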### Randomisation and concealment

Patients will be randomised using a centralised web-based system (SCRAM) hosted by Sheffield CTRU, which has user-restricted functionalities granting access rights to specific areas as appropriate. The sequence will be computer generated using permuted block randomisation stratified by recruiting site and severity of OHSS. Block sizes will be disclosed during dissemination of findings and only the randomisation (trial) statistician(s) not involved in the recruitment process will know the block sizes during the trial. The trial statistician will generate the randomisation sequence; however, they will not have access to the generated sequence. Research staff at recruiting centres will use a web-based computer system with restricted access rights to enter participant details; randomisation outcome will then be revealed. Re-randomisation will not be permitted.

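### The final primary analysis ignores the factors that randomisation is stratified on; it is valid and meets the planned power, but its interval is too wide if severity or site predicts admission

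*Protocol article*

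**What the plan says.** Under Randomisation and concealment, the allocation sequence is "computer generated using permuted block randomisation stratified by recruiting site and severity of OHSS".

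Under Statistical analysis, the absolute difference in admission rates is the primary effect measure, and the final analysis is fixed: "For the final analysis of the primary outcome, the unadjusted difference in hospitalisation rates with CI obtained via normal approximation will be reported", together with the "p value from a χ^2^ test". The adjusted analysis has the lesser role: "For sensitivity analysis, a mixed effects logistic regression model adjusted for stratification factors", with site random and severity fixed, and the risk difference obtained through margins and the delta method. That sentence stands between the interim and final-analysis sentences; I read it as covering the final analysis too.

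Elsewhere in the section the stratification factors are used: "For progression of OHSS severity, a mixed effects logistic regression model adjusted for stratification factors". Satisfaction and the subgroup models of the primary outcome also adjust, and the bootstrap for length of stay accounts for stratification. Time to resolution does not: "differences qualified using a log-rank test", with no stratification mentioned.

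**The concern.** Blocks stratified by site and severity keep the arms nearly balanced on both. If either factor predicts admission, the difference in rates varies less from trial to trial than it would under simple randomisation. The usual two-sample variance and the chi-squared test do not know this. They charge the comparison for between-stratum variation that the design has removed, so the interval is too wide and the p value too large on average.

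Severity is a plausible predictor here. The Introduction describes usual practice as watching the patient and admitting her once the condition is severe. At stake is the precision of the headline result. The trial wants evidence that can change practice whichever way it falls, so interval width matters for a null result as well as a positive one.

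**Working it through.** **Inputs from the article (Sample size and interim analyses; Recruitment).** UC rate 41%, target 21%, one-sided 2.5% (two-sided 5%), 90% power, 112 per arm, interim at 73 per arm, futility threshold 4.5 points, about 20 sites.

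**Assumed, because the article does not give them.** Admission rate by severity, share severe, between-site variation (ICC) and block size.

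**1. The plan's own figures, unadjusted.**
- n per arm = [1.96·√(2·0.31·0.69) + 1.2816·√(0.41·0.59 + 0.21·0.79)]² / 0.20² = (1.282 + 0.818)² / 0.04 ≈ 110.3, so 111 against 112 stated.
- Power at 112 per arm is 90.4% with a fixed sample and 90.1% with the futility look.
- Chance of stopping under the target effect: Φ((0.045 − 0.20)/√(0.4078/73)) = Φ(−2.07) = 1.9%, as stated. Under no effect, the exact binomial gives 72.2%, as stated.

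The sample size was therefore set for the unadjusted comparison.

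**2. Severity alone, by hand.** Assume half are severe, UC rates of 26% (moderate) and 56% (severe), and a 20-point fall in each stratum.
- Within-severity variance: UC (0.1924 + 0.2464)/2 = 0.2194; OP (0.0564 + 0.2304)/2 = 0.1434; sum 0.3628.
- Variance used by the unadjusted analysis: 0.2419 + 0.1659 = 0.4078.
- Ratio 0.3628/0.4078 = 0.89, so the SE is √(1/0.89) ≈ 1.06 times what it should be. The 95% half-width is 1.96·√(0.4078/112) = 11.8 points against 1.96·√(0.3628/112) = 11.1.
- Severity gaps of 20 and 40 points give ratios of 0.95 and 0.80.
- With the same UC rates but a constant odds ratio for treatment, the ratio is about 0.92 (SE about 4% too wide).

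**3. Severity and site together.** True SE = √[(W_UC + W_OP)/112 + V/224], where W is the mean within-stratum p(1 − p) and V is the variance of the treatment effect across strata. The unadjusted SE is √(0.4078/112) = 0.0603 throughout. Power is Φ((0.20 − 1.96·SE₀)/SE_true) unadjusted, with SE₀ = √(2·0.31·0.69/112), and Φ(0.20/SE_true − 1.96) adjusted. With 40% severe:

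| Site ICC | Severity OR | UC rate, moderate/severe | SE ratio | Half-width, unadjusted v adjusted | Power, unadjusted v adjusted |
|---|---|---|---|---|---|
| 0 | 1 | 41/41% | 1.00 | 11.8 v 11.8 | 90.4 v 91.2% |
| 0.05 | 3 | 31/56% | 1.05 | 11.8 v 11.3 | 91.4 v 93.4% |
| 0.10 | 5 | 27/62% | 1.09 | 11.8 v 10.8 | 92.3 v 95.2% |
| 0.10 | 10 | 22/70% | 1.15 | 11.8 v 10.3 | 93.4 v 96.8% |

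The 0.8-point gap in the first row is not a gain from adjustment. It comes from a pooled variance in one formula and an unpooled one in the other, and it forms part of the gap in the other rows. With 20% or 50% severe, the largest SE ratios are 1.13 and 1.14.

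**4. Simulation** (4,000 trials per scenario, 20 sites, blocks of 4, 40% severe; chi-squared test against a linear model for site and severity with robust SE).
- Strata not prognostic: power 90.6% unadjusted v 90.2% adjusted, so no gain.
- ICC 0.05, OR 3: two-sided type I error 3.7% v 4.5%; power 91.5% v 93.1%.
- ICC 0.10, OR 5: type I error 3.3% v 4.7%; power 91.6% v 94.0%.

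In the last scenario under the target effect, the two estimates vary almost equally (empirical SE 0.0571 and 0.0567). The loss thus lies mainly in the reported SE, not in the point estimate. The mean unadjusted SE of 0.0600 is 0.0600/0.0571 = 1.05 times the empirical value, below the 1.09 from the formula, which assumes perfect balance within strata. The large-sample ratios are therefore best read as upper values.

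**The case against.** The strongest reply is that nothing is broken. The sample size was set for the unadjusted test, that test delivers the stated 90% power, and its type I error does not exceed 2.5% one-sided. This stands. A reader might infer a power shortfall or an invalid test; the article's figures show neither.

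Second, the size rests on inputs that the article does not contain. This also stands. A reader might take the Introduction to say that severe cases are the ones admitted. It describes usual practice, not an admission rule for enrolled women. The exclusion criteria under Recruitment also remove those whose pain or vomiting requires hospitalisation and those ill enough for high-dependency care. Severity may therefore predict admission less strongly among those randomised.

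Third, the adjusted result will be reported anyway, and different adjustment for primary and secondary outcomes is not in itself a contradiction. Both are fair. What remains is which of two prespecified analyses carries the headline interval and p value.

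Fourth, the adjusted model has its own demands. With 224/20 ≈ 11 women per site it may not converge. With a random site effect, margins can give a site-conditional rather than a population-averaged difference. The calculations above used a linear model as a stand-in and did not run the mixed logistic model itself. These points shape the remedy but do not remove the reason for it.

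Fifth, the log-rank point concerns a secondary outcome, has no magnitude attached, and the article leaves sensitivity and alternative approaches there to the SAP. It is optional.

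**Conclusion.** The point holds as one of efficiency. Randomisation uses site and severity, and the primary interval and p value do not. If neither factor predicts admission, nothing is lost. If they do, the unadjusted analysis is conservative: over site ICC 0 to 0.10, severity OR 1 to 10 and 20 to 50% severe, the SE is about 0 to 15% too wide, and about 0 to 3.5 points of available power are given up. Those ranges are assumptions, and the upper ends need strong prognostic strength. The loss is measured against what an adjusted analysis could deliver, not against the planned 90%. The change is worth making because the model is already planned and the sample size, effect measure and interim rule stay as they are.

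**What to change.** Before unblinded data are accessed, amend the protocol and SAP wording as follows.

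- **Primary final analysis:** the stratification-adjusted marginal (population-averaged) risk difference with its 95% CI and p value, from the mixed logistic model already planned. State that margins are averaged over the site effect.
- **Fallback:** a severity-stratified Mantel-Haenszel risk difference, prespecified for non-convergence.
- **Sensitivity analysis:** the unadjusted difference with its normal-approximation interval and the chi-squared test.
- **Interim:** keep the futility rule on the unadjusted difference, so that the 1.9% and 72.2% stopping probabilities still apply.
- **Stagewise ordering:** state which final estimate, adjusted or unadjusted, the median unbiased estimate accompanies.
- **Optional:** stratify the log-rank test by severity.

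No extra data or participants are needed. The cost is the added specification and reliance on a model with about 11 women per site.

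### At the trial's planning rates the bootstrapped median difference in cumulative hospital stay is very likely to be 0 and uninformative about bed-days

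*Protocol article*

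**What the plan says.** The protocol article lists "Cumulative length of OHSS-related hospitalisation" as a secondary outcome (Outcomes). For its analysis, the Statistical analysis section says a "bootstrapping resampling procedure (accounting for stratification) will be used to obtain the median difference with 95% CI and associated p value". It names no analysis population for this outcome, does not limit it to admitted women, and adds no mean difference or two-part analysis. Intention to treat is stated for the primary analysis.

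The expected admission rates are in Sample size and interim analyses. Under current care "the mean OHSS-related hospitalisation rate is approximately 41.2% (26/63"), from an audit "over a year (95% CI 29.0% to 54.4"%). The design assumes "41% UC hospitalisation rate, 0% drop-out rate, a 20% reduction in hospitalisation rate", with a "maximum total sample size of ~224 (112 per arm"). These rates relate to the primary outcome, "OHSS-related hospitalisation for at least 24 hours within 28 days of randomisation". The length-of-stay outcome carries no 24-hour minimum.

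**The concern.** A woman who is never admitted contributes zero days. If more than half of an arm has zero days, that arm's median is 0, however long the others stay. The planning rates put both arms in that position, and a successful intervention pushes the OP arm further into it. A difference of medians would then be 0 for small and large effects alike, and the bootstrap distribution behind the interval and p value would have most of its mass at 0.

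At stake is the reading of one listed secondary outcome. A real saving in hospital days could be published as a median difference of 0 and taken to mean no effect on length of stay.

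**Working it through.** **Inputs.** From Sample size and interim analyses: UC 41%, reduction 20 points (so OP 21%), 112 per arm, no drop-out, 90% power, one-sided 2.5%. The documents give no length-of-stay data, so any stay distribution below is an assumption.

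**The plan's own figures.**
- The pooled two-proportion formula uses a mean rate of 0.31: n = [1.96·√(2·0.31·0.69) + 1.2816·√(0.41·0.59 + 0.21·0.79)]² / 0.20² = (1.282 + 0.818)² / 0.04 ≈ 110.3, so 111 per arm. At 112 per arm, power is 90.4%. This agrees with the stated 224.
- The exact interval for 26/63 is 29.0% to 54.4%, as stated.

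**Share with zero days.** UC: 1 − 0.41 = 59%. OP: 1 − 0.21 = 79%.

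**Chance that a sample median is 0.** With 112 women the median is the average of the 56th and 57th ordered values. It is 0 only if at least 57 values are zero, that is, if at most 55 women have a stay.
- UC: P(X ≤ 55), X ~ Bin(112, 0.41) = 0.966. So the UC median exceeds 0 (56 or more admitted) with probability 3.4%.
- OP: P(X ≤ 55), X ~ Bin(112, 0.21) ≈ 1.000.
- Both: 0.966 × 1.000 = 96.6%.

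**The same calculation at other rates.**

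| UC v OP | P(both medians 0) |
|---|---|
| 29% v 9% | above 99.99% |
| 41% v 1% | 96.6% |
| 41% v 36.5% | 96.4% |
| 41% v 41% | 93.4% |
| 45% v 25% | 83% |
| 50% v 30% | 46% |
| 54.4% v 34.4% | 15% |

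With UC at 41%, the result hardly moves between no benefit and near-complete prevention of admission.

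**If the median of all pairwise differences (OP minus UC) is meant.** Both zero: 0.59 × 0.79 = 46.6%. Assume the same stay distribution among admitted women in both arms, so that pairs in which both are admitted (0.41 × 0.21 = 8.6%) split evenly. Then below zero is 0.41 × 0.79 + 0.043 = 36.7%, and above zero is 0.59 × 0.21 + 0.043 = 16.7%. The 50th percentile falls among the zeros, so this estimate is also 0.

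**Simulation.** Assumed stay among admitted women: 1 + exponential, mean 4 days; 500 unstratified bootstrap resamples per trial.
- At 41% v 21%, two runs (300 and 400 trials) gave a median difference of exactly 0 in 95% and 98.5% of trials. The interval was exactly [0, 0] in 48% and 46%, and excluded 0 in none.
- On such data the bootstrapped mean difference excluded 0 in about 65% of trials. With an assumed gamma-shaped stay this was 79%, so the gain depends on the stay distribution. The median difference was 0 in 97% of trials under that assumption too.
- With equal admission (41% v 41%) and mean stay halved from 4 to 2 days under OP, the median difference was still 0 in 92% of trials.
- At 50% v 30% the median's interval excluded 0 in about 3% to 4% of trials; at 54.4% v 34.4%, in about 17% to 18%.

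**What the mean would show.** Difference = mean stay × (0.21 − 0.41). At an assumed mean stay of 2, 4 or 6 days per admitted woman, this is −0.4, −0.8 or −1.2 days per randomised woman.

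**The case against.** Four points on the other side deserve an answer.

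- **The UC share is uncertain.** A reader might infer that the estimate is 0 by construction, whatever OP does. The documents do not support that. The audit interval reaches 54.4%. The 41% counts stays of at least 24 hours, while this outcome has no such threshold. Intervention and control also says that overnight stays caused by fluid administration do not meet the primary outcome, and these might still count as hospital days here. About 9 more points would bring the UC share to half, and a harm that took OP admissions past half would move the OP median. All of this stands, so the conclusion is conditional. It does not rescue the measure, because the simulated chance of an interval excluding 0 stayed low at 50% and at 54.4%.
- **The population is not stated.** If only admitted women were analysed, the zeros would vanish. The article does not say this. Such a comparison would be between groups selected by the primary outcome, not by randomisation.
- **Detail is left to the SAP, which is not shown.** The SAP may well define the population. The effect measure, however, is already stated in the article, and the point concerns that choice.
- **Cost.** A reader might infer that the cost analysis would miss a saving in bed-days. Nothing shown supports this. The Health economics section collects hospital admission data, applies unit costs and reports incremental costs separately, and does not use the median difference.

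**Conclusion.** The point holds in conditional form. At 41% v 21%, with all randomised women included and no shorter stays counted, both sample medians are 0 in about 97% of trials, and the planned estimate is very likely 0 and uninformative about bed-days. This follows from the planning rates and the sample size and needs no assumption about length of stay. The figures for interval behaviour and for the gain from using the mean do rest on assumed stay distributions.

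The problem weakens as the UC share with any stay nears or passes half: the chance that both medians are 0 is 46% at 50% v 30% and 15% at 54.4% v 34.4%.

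Severity is moderate. This is one secondary outcome. The primary outcome and the health economic analysis are unaffected.

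**What to change.** In the protocol and the SAP, replace the median difference by the difference in mean cumulative OHSS-related hospital days over all randomised women, counting zero for those never admitted. Keep the same stratified bootstrap for the 95% confidence interval and p value. Report per cent admitted and length of stay among admitted women descriptively by arm.

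State whether stays under 24 hours and overnight stays for fluid administration count towards the total.

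The cost is a small change of wording and of the statistic in the bootstrap code, to be made before unblinded data are accessed. The downside is that a mean is more sensitive to a few long stays. A rank-based or two-part analysis over all randomised women is a possible alternative, but the mean difference reads directly as bed-days.
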